### Inclusion criteria

Persons at a high risk of falling shall meet at least two of the following requirements:They have fallen at least once over the last 12 months.They required more than 15 s to complete, or require support in, the TUG test.They obtained a mean CDP SOT balance score of < 68%.They have fallen at least once in the CDP SOT.They obtained a score in Vertiguard’s gSBDT of > 60%.

### Exclusion criteria

Cognitive decline or reduced cultural level that prevents the patient from understanding the assessment, undertaking the vestibular rehabilitation exercises and providing informed consent.Organic conditions that prevent the patient from standing on two feet, which is necessary for the assessment of balance and performance of VR exercises.Balance disorders caused by conditions other than age (neurological, vestibular, etc.).Undergoing treatment which may have an effect on balance.

### Calculation of sample size

The sample size was estimated after consulting the results of previous studies conducted by the group [24] in which there was a 10-point change in the mean balance CDP SOT (baseline value: 64; post-rehabilitation value: 73; value after 12 months: 74). We considered that a security level (1-ά) of 95% and a type II (β) error likelihood of 0.2, 53 subjects are needed for each arm. The sample size will be 212 subjects; it will be increased to 220 (55 for each arm) in case of any loss to follow-up.

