## Methods and design

### Aim of the study

The primary objective is to evaluate the effectiveness of a mobile posturographic system with vibrotactile neurofeedback to improve balance in elderly patients. Each subject was assessed immediately after the rehabilitation.

The secondary objectives are:To verify that improvements in balance are maintained in the medium term (six to twelve months).To consider whether this improvement in balance results in a reduction in the number of falls suffered by the elderly.To assess whether the reduction in the number of vestibular rehabilitation sessions (five) leads to similar results (an improvement in balance and a reduction in the number of falls) to those obtained after ten sessions. Both rehabilitation systems are compared using computerised dynamic posturography and mobile posturographic with vibrotactile neurofeedback.

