#### Bivariate analysis

We will provide the differences (95% CI) in the balance test assessments between baseline and end of intervention, and 6 months and 12 months post-intervention. These measures will be compared between groups by ANOVA or the Kruskall-Wallis test if normality is not assumed.

The Chi-squared test or Fisher’s exact test, depending on the conditions, will be used to analyse the number of falls occurring from 12 months prior to inclusion and 12 months post-intervention.

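### The 80% power rests on a before-after gain within patients, so it is unsupported for the planned between-arm comparisons; the 10 points is also the 12-month gain, not the post-rehabilitation gain of 9

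*Protocol article*

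**What the plan says.** Under Calculation of sample size, the protocol article takes its effect from previous work by the group, in which "there was a 10-point change in the mean balance CDP SOT (baseline value: 64; post-rehabilitation value: 73; value after 12 months: 74". It sets a "security level (1-ά) of 95" percent and a type II "error likelihood of 0.2, 53 subjects are needed for each arm". This gives 212 patients, raised to 220 (55 per arm) for losses. The section names no test or contrast and gives no difference between arms.

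The rest of the article fixes the setting:

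- **Arms** (Randomisation and intervention): all four are active, formed by two devices and by five or ten sessions of each.
- **Questions** (Background): five versus ten sessions, and one device versus the other. Aim of the study makes the effectiveness of the mobile system the primary objective and puts the session and device comparisons among the secondary ones.
- **Primary timing** (Aim of the study, directly after the primary objective): "Each subject was assessed immediately after the rehabilitation".
- **Tests** (Bivariate analysis): changes from baseline are estimated with 95% confidence intervals, and then "These measures will be compared between groups by ANOVA", or by a rank test if normality is not assumed.

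**The concern.** A power statement belongs to one effect, one comparison and one time point. Here the effect is how far treated patients improve over time. The device and session questions ask how far the improvement differs between two treated groups. The first quantity gives no information on the second.

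The time point does not match either. The figure called a 10-point change is the 12-month gain, while the primary assessment is at the end of rehabilitation.

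This matters most for five versus ten sessions. There the investigators hope for similar results, and the Discussion would halve cost on that basis. A non-significant difference is therefore the welcome outcome. With 80% power attached to the trial, it could be taken as evidence of similarity, although the sizing paragraph states no between-arm difference.

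**Working it through.** **Inputs from the protocol article.** Baseline 64, post-rehabilitation 73, 12 months 74; alpha 0.05; power 0.80; 53 per arm; four equal arms. Two-sided testing is assumed. The SD is not shown, so every SD below is an assumption.

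**1. The plan's own figures.** 4 × 53 = 212 and 4 × 55 = 220 are correct. The gains are 73 - 64 = 9 at the end of rehabilitation and 74 - 64 = 10 at 12 months. The 53 cannot be reproduced without an SD, but the SD that would produce it can be found:

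- *Two-sample reading.* n per arm = 2 × (SD × 2.80 / difference)², where 2.80 = 1.96 + 0.84. With n = 53 and 10 points, SD = 10 × √(53/2) / 2.80 = 18.4. The exact t-test gives 18.2.
- *Paired before-after reading.* n = (SD of change × 2.80 / change)². With n = 53 and 10 points, SD of change = 10 × √53 / 2.80 = 26.0. The exact t-test gives 25.5.

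**2. Using 9 in place of 10.** If 10 was entered and all else is kept, n scales by (10/9)²: 53 × 1.235 = 65.4. The exact two-sample calculation gives 65.2, so 66 per arm. With 53 per arm, power at 9 points is 71%, on the two-sample and the paired reading alike. If 9 was in fact entered, the implied two-sample SD is 16.4 and 53 per arm does give 80% at 9 points.

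**3. What the design can detect between arms.** For a two-sided 5% two-sample t-test, the difference detectable with 80% power is 0.549 × SD for 53 versus 53 and 0.387 × SD for 106 versus 106. The second is the pooled contrast: both arms of one device against both of the other, or both five-session arms against both ten-session arms.

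| Assumed SD | Single pair, 53 vs 53 | Pooled, 106 vs 106 |
|---|---|---|
| 8 | 4.4 points | 3.1 points |
| 10 | 5.5 points | 3.9 points |
| 15 | 8.2 points | 5.8 points |
| 18.2 (implied by the two-sample reading) | 10.0 points | 7.0 points |

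On the two-sample reading, then, 80% power applies to a pair of arms that differ by as much as the whole gain of the earlier study. At that SD, power for a 5-point difference between two arms is 29%. At SD 8, a 4.5-point difference has 82% power with 53 per arm; at SD 10 it has 90% in the pooled contrast.

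**The case against.** The strongest reply is that the sizing may match the primary objective. That objective concerns the effectiveness of the mobile system and can be read as a before-after question; the analysis section does plan intervals for the change from baseline. The sample-size section does not exclude this reading, and on it a within-patient change is the right kind of effect. This stands. But the 80% then belongs to the within-arm change and does not carry over to the device or session contrasts.

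A second reply is that the article prints all three values, follows patients for 12 months and models all post-treatment visits, so 10 is a true figure for one visit. That also stands, and it makes the 9-versus-10 part minor. The figure still does not match the primary time point.

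A third is that SD, test and sidedness are details an article may leave to the full protocol. Agreed: their absence is not held against the plan. The point rests on the effect that is stated.

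Three stronger readings are not supported:

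- *The trial is underpowered for its between-arm questions.* No SD is shown. With SD 8 to 10, the detectable differences are well below the earlier gain, and lower still when arms are pooled.
- *A 10-point difference between arms means that one programme does nothing.* That follows only if the better arm gains exactly 10; gains of 13 and 3 also differ by 10.
- *The trial needs 66 per arm.* That holds only if 10 was the value entered and 80% power at 9 points is the target.

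**Conclusion.** The point holds as one of unsupported power, not of low power. The stated 80% rests on a within-patient change, the comparison sized is not identified, and no between-arm difference is given. It therefore cannot be claimed for the device or the five-versus-ten contrast. This conclusion needs no SD.

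The time-point mismatch follows from the protocol's own figures: 9 at the primary assessment, 10 at 12 months. Its size, 71% instead of 80% power or 66 instead of 53 per arm, assumes that 10 was entered.

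True between-arm power is unknown. Over SDs from 8 to 18.2, the detectable difference runs from 4.4 to 10.0 points for a pair of arms and from 3.1 to 7.0 for the pooled contrasts. These figures assume two-sided 5% tests with no multiplicity adjustment and 53 evaluable patients per arm.

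**What to change.** Keep 220 patients and rewrite the sample-size paragraph:

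1. Label 9-10 points as a gain within treated patients, and use 9 for the post-rehabilitation time point.
2. State which contrast the 80% refers to, and withdraw it for the others.
3. Give the detectable difference for single pairs of arms and for the pooled device and session contrasts, using the SD from the earlier study. The table above shows the form; its SDs are placeholders.
4. State that a non-significant five-versus-ten result will not be read as similarity on the strength of the 80%.

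The cost is a change of wording, with no extra patients or visits. The downside is that the stated power may look less favourable.

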### Randomisation and intervention

#### Visit 1

After the first screening visit, the patients who provided consent will be included in the study and randomised to one of the following study arms:A.**Intervention with dynamic computerized posturography exercises (ten sessions)**. The Smart Equitest program was used: 10 exercises per session, which were customized depending on each patient’s deficit (as observed in the earlier postural study), were undertaken. The exercises involve visual biofeedback together with sensitive, real-time monitoring of movement. For some exercises, patients must maintain their centre of gravity (COG) over the base of support, while for others the COG must be moved to a series of targets. In addition, the support surface and/or visual surround may also move in response to the patient’s own movement. The exercise difficulty was progressively increased throughout the rehabilitation sessions by increasing the LOS, the transition rate or the movement of the posturography platform. The duration of each session was approximately 15 min. The distribution of sessions was one per day and five per week (two weeks)B.**Intervention with dynamic computerized posturography exercises (five sessions)**. Same as Group A, except for the number of sessions (5) and their distribution (one session on alternate days, for two weeks).C.**Intervention with mobile posturography (Vertiguard) exercises (ten sessions)**. As many as six tasks were set, and the most prominent deviations from normative control values were included in the training programme. Individual feedback was stored in the device for each patient based on body sway analysis. Training was performed using the training function of Vertiguard-RT device. This neurofeedback system contains a battery-driven main unit which is fixed on a belt at the centre of the body mass (hip) and one vibration stimulator on the front, back, left and right side, respectively. Vibration stimulators are mounted on the same belt as the main unit. They were adjusted by sliding them over the belt to the correct position for the individual patient. The main unit continuously determines the Coriolis force during body movements (pitch and roll) using inbuilt gyroscopes and compares those values with individual pre-set thresholds for stimulator activation in specific directions.Training was performed daily under the supervision of a physician over 2 weeks (over 10 sessions and the weekend was excluded). A training session consisted of 5 repetitions of six selected training tasks as described above (each repetition lasted 20 s or until the movement was finished). The patient received a vibrotactile feedback signal during training for those directions when a body sway higher than pre-set thresholds was noted. Vibration was reinforced with increasing sway: the more it exceeded the pre-set values, the stronger the vibration was at the corresponding site.No vibrotactile feedback was applied if the patient’s sway was below pre-set thresholds. The exercise difficulty progressively increased throughout the rehabilitation sessions by pressing the sensitivity buttons (up/down) on the main unit. During this procedure, the individual pre-set thresholds were similarly decreased for all sway directions of the specific training conditions until the patient perceived a vibration while performing the training task.D.**Intervention with mobile device Vertiguard exercises (five sessions)**. Same as Group C, except for the number of sessions (5) and their distribution (one session on alternate days, for two weeks).

Randomisation will be performed by C.H.U de Santiago Clinical Epidemiology and the Biostatistics Unit, following the same strategy than in our previous clinical trial [14].

### Variables

The study variables shall be as follows:Date of birth.Sex.Weight (kg) and height (cm).Number of falls in the 12 months before inclusion.Hospitalisations due to falls over the previous 12 months.Percentage of mean balance (average) as observed in computerized dynamic posturography (CDP) sensory organisation test (SOT) (PRIMARY ENDPOINT); this will be obtained by calculating the mean of the scores of the 18 records of each sensory organisation test (calculated by software).DHI score: covered by patient.Short FES-I score: covered by patient.Duration (seconds) of TUG: measured by evaluator.Number of steps in TUG: measured by evaluator.Number of supports in TUG: measured by evaluator.Mean value of CDP SOT condition 5: calculated by software.Mean value of CDP SOT condition 6: calculated by software.CDP SOT vestibular contribution value: (mean value of condition 5/mean value of condition 1) × 100.Mean value of directional control of limits of stability in CDP: calculated by software.Mean endpoint value and maximum travel point of limits of stability in CDP: calculated by software.Vertiguard gSBDT value: calculated by software.Number of falls over 12 months after completion of VR programme (we will give the patient a timetable to allow them to check each fall immediately after it happens, in order to avoid memory bias).Hospitalisation resulting from those falls: date, diagnosis, duration of hospitalisation.

### Data collection and ethics

The balance study undertaken in the first visit (**baseline record**) is repeated, with all the tests (questionnaires, TUG test, CDP SOT, CDP limits of stability and Vertiguard record) three more times:

● Visit 2.- Immediately after completion of VR.

● Visit 3.- Six months after VR.

● Visit 4.- Twelve months after VR.

The data will be collected in a specially designed database. There will be periodic data quality controls. The PI will monitor the study and ensure that the data are authentic, accurate and complete, and that the subjects’ safety and rights are protected.

The protocol has been approved by the Independent Ethics Committee of Galicia (protocol 2014/411).

The study will be conducted according to ICH Good Clinical Practices (GCP), the Declaration of Helsinki and Law 14/2007, of 3 July, on Biomedical Research.

### Study timeline

The study is running from January 2016 to December 2019 (Fig. 1).

**Fig. 1 Fig1:**
[figure not shown]
Standard protocol items: recommendations for interventional trials (SPIRIT) figure

### Analytical plan and statistical measures

The patients’ demographic data and characteristics will be described globally and by the covariables of interest, as will the patients’ results.

The continuous results will be summarised as mean, median, standard deviation (D) and interquartile range (P25, P75). For the categorical results, we will present the number and percentage of patients in each category.

The statistical analyses will be based on the complete analysis group (CAG), which comprises all the subjects (those who granted informed consent and met all the inclusion and exclusion criteria, and were randomised to one of the study arms).

**The outcomes** of interest are: balance assessment (average balance score in CDP SOT and Vertiguard’s gSBDT score, with possible values 0–100 in both); assessment of instability perception scales (DHI, short FES-I) on visits 2 (after intervention), 3 (6 months after intervention) and 4 (12 months after intervention); number of falls at 12 months post-intervention.

**The covariables of interest** are:Baseline patient characteristics: they include the variables specified for visit 0.Associated risk factors: age, sex, weight (kg), height (cm), previous falls (yes/no).Adherence to intervention (investigator’s direct observation).

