**Methods:**

*Design*: randomized controlled trial. It is an experimental study, single-center, open, randomized (balanced blocks of patients) in four branches in parallel, in 220 elderly patients with high risk of falls; follow-up period: twelve months. *Setting*: Department of Otorhinolaryngology of a tertiary referral hospital. *Participants*: people over 65 years, fulfilling two or more of the following requirements: a) at least one fall in the last twelve months. b) take at least 16 s or require some support in perform the “timed up and go” test. c) a percentage of average balance in the sensory organization test (SOT) of the CDP < 68%. d) at least one fall in any of the conditions in SOT-CDP. e) a score in Vertiguard’s gSBDT > 60%. *Intervention*: Four differents protocols of vestibular rehabilitation (randomization of the patients). *Main outcome measure*: The percentage of average balance in the SOT-CDP. *Secondary measures*: time and supports in the “timed up and go” test, scores of the CDP and Vertiguard, and rate of falls.

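### The abstract lists a fall rate, but the body defines a 12-month number of falls and fixes a test that cannot use observation time

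*Protocol article*

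**What the plan says.** All references are to the protocol article.

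- **Abstract, Methods.** The main outcome is balance: "The percentage of average balance in the SOT-CDP". Falls come last among the secondary measures: "scores of the CDP and Vertiguard, and rate of falls".
- **Aim of the study.** A secondary objective is "To consider whether this improvement in balance results in a reduction in the number of falls suffered by the elderly". The comparison of five with ten sessions also refers to the number of falls.
- **Variables.** The fall variable is "Number of falls over 12 months after completion of VR programme". Patients mark each fall on a timetable when it happens.
- **Analytical plan and statistical measures.** The fall outcome is "number of falls at 12 months post-intervention". The analysis set is all consenting, eligible, randomised subjects.
- **Bivariate analysis.** A Chi-squared or Fisher's exact test "will be used to analyse the number of falls occurring from 12 months prior to inclusion and 12 months post-intervention".
- **Multivariate analysis.** The only regression model is Gaussian and concerns balance. Falls are not in it.
- **Calculation of sample size.** The total is raised from 212 to 220 "in case of any loss to follow-up".

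None of these sections gives a time denominator for falls, or says how a patient observed for less than 12 months is counted.

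**The concern.** A number of falls and a rate of falls are the same quantity only when everyone is observed for the same time. The plan expects that some patients will not be, and it keeps all randomised patients in the analysis set. The named test has no place for observation time. It also works on categories, so a count has to be grouped before the test can be applied, and no grouping is stated. As written, the analysis cannot estimate the rate that the abstract lists.

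At stake is the fall-reduction objective. The year before inclusion is a full 12 months for every patient, while the year after rehabilitation is shorter for anyone who leaves. If shortened counts were entered as 12-month counts, leaving would look like falling less. If leavers were dropped and frailer patients left more often, the remaining patients would fall less than the randomised group. Unequal loss between arms would carry either effect into the comparison of arms.

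**Working it through.** **1. The plan's own allowance.** From the sample size section: 4 × 53 = 212, and 220 / 4 = 55 per arm. The allowance is 220 − 212 = 8 patients, or 8/220 = 3.6%. Shared equally it is 2 per arm, or 2/55 = 3.6%. This is the only loss figure that the document yields.

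**2. Model.** Assume no true effect on falls, a constant fall rate, leaving unrelated to falling, and departures spread evenly over the year. A leaver is then observed for half a year on average. With loss fraction L, mean observed time is 1 − L/2 years. An untimed count is therefore too low by L/2.

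**3. After against before, at the implied loss.** 0.036/2 = 0.018, so the year after rehabilitation is understated by about 1.8%. The timing of departures is an assumption. If all leavers left on the last day the figure would be 0, and if all left on the first day it would be 3.6%.

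**4. Between arms.** The apparent count ratio with equal true rates is (1 − L₂/2)/(1 − L₁/2).

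| Loss, arm 1 | Loss, arm 2 | Status | Apparent ratio |
|---|---|---|---|
| 3.6% | 3.6% | allowance shared equally | 1.000 |
| 0% | 3.6% | assumed split | 0.982 |
| 0% | 8/55 = 14.5% | all 8 allowed losses in one arm | 0.927 |
| 5% | 15% | assumed | 0.925/0.975 = 0.949 |
| 5% | 25% | assumed | 0.875/0.975 = 0.897 |

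With person-time as denominator, the expected rate ratio under this model is 1.00 in every row.

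**5. On a faller/non-faller scale.** This is one way in which the named test could be applied. The Background section gives yearly risks of about one-third over age 65 and one-half over age 85, used here only as illustration. With λ = −ln(1 − p), an evenly spread leaver is seen to fall with probability 1 − p/λ, which is 0.178 for p = 1/3 and 0.279 for p = 1/2. At 14.5% loss in one arm:

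- p = 1/3: 0.8545 × 0.333 + 0.1455 × 0.178 = 0.311, or 2.3 points low
- p = 1/2: 0.8545 × 0.500 + 0.1455 × 0.279 = 0.468, or 3.2 points low

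**6. If loss is related to frailty.** Assume frailty with mean 1 and variance 1, and loss probability proportional to frailty, at L = 10%. None of these values comes from the document.

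- Completers only: mean count (1 − 2 × 0.10)/(1 − 0.10) = 0.889 of the true value.
- Person-time: (1 − 0.10)/(1 − 0.05) = 0.947 of the true value.

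Under these assumptions person-time removes about half of the bias, not all of it.

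**The case against.** The strongest reply is that this is a matter of wording. The Variables section fixes the window at 12 months, so for every completer the count is the yearly rate. The body uses the number consistently, and the abstract may be loose shorthand. Handling of incomplete follow-up is commonly left to the full protocol or SAP, which are not shown. At the only loss the document implies, the effect is about 2%.

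Much of this stands, and it rules out several stronger readings that a reader might infer:

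- *That the rate of falls is the trial's outcome.* It is one of several secondary measures; the main outcome is SOT balance.
- *That the fall analysis is biased as written.* The article does not say that a partial count is entered as a 12-month count, nor that leavers are dropped.
- *That the net bias must favour a reduction.* The limitations in the Discussion concede possible memory bias for falls before inclusion and plan checks with relatives and medical records. Falls afterwards are marked as they happen. Under-recall of earlier falls would tilt the comparison towards an apparent increase.
- *That the arm losing more patients will look better.* This needs unequal loss, and nothing in the document predicts that or says that frailer patients leave more often.

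What the reply does not remove is the choice of test. That is a stated commitment, not a detail left for later. Chi-squared and Fisher's exact tests cannot use observation time, whatever rule for leavers is written elsewhere, so they cannot deliver the rate named in the abstract.

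**Conclusion.** The point holds as an inconsistency of definition together with a poorly fixed test. The abstract lists a rate, the body defines a number, and the named test cannot use the time element that separates the two once some patients leave early.

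The consequence is a conditional risk to a secondary outcome. If shortened counts are used, the year after rehabilitation is understated by about 1.8% at the implied 3.6% loss, with no between-arm bias if loss is equal. The understatement is about 7% in one arm if all eight allowed losses fall there. These figures assume evenly spread departures unrelated to falling. Larger, more unequal or frailty-related losses are illustrations without support in the document, and the net direction of the before-after comparison is not established. The size is modest, but the correction is cheap and uses information that the timetable already collects.

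**What to change.** - **One definition** in the abstract, Variables, Analytical plan and Bivariate analysis: falls per person-time from the end of rehabilitation to 12 months, death or last contact, whichever comes first.
- **Data.** Record the last date covered by each patient's fall timetable.
- **Analysis.** Replace the Chi-squared/Fisher analysis of the number of falls with a negative binomial (or overdispersed Poisson) regression by arm, with log observed time as offset and prior-year falls as covariate. The test must be replaced because it takes no offset.
- **Reporting.** Give person-time by arm beside the number of falls.

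Cost: one extra date per patient and slightly more analysis work. The apparent reduction in falls may become smaller. Some bias remains if loss is related to frailty, so losses by arm should be shown with the result.

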#### Multivariate analysis

In order to analyse the efficacy of the intervention in improving balance from the baseline, considering each subject’s repeated measures (visits 2, 3 and 4) and the covariables of interest, we will use mixed linear models (using Generalised Estimation Equations, GEE) when treatment is a fixed factor, the CDP SOT percentage mean balance at baseline and over time post-intervention is a random effect and a Gaussian distribution function is considered.

All the data analyses will be performed using R software, version 2.9.1 [25].

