It is also possible to implement two strategies that improve the cost-benefit of posturography. The first involves optimising the number of rehabilitation sessions. Although this number must be adjusted to the specific needs of each patient, the average is approximately 10. However, in certain patients who suffer from instability due to unilateral vestibular balance deficits, regardless of age, it has been proven that groups of five and of ten session programmes both have similar effects [16]. These data are, obviously, not directly extrapolate to elderly patients with instability, because in cases due to unilateral vestibular dysfunction, the deficit lies in only one labyrinth, and the deficit can be compensated with the remaining relevant sensorial systems (the other labyrinth, sight and the proprioceptive system) more easily. Age-related balance deficits, however, generally have multiple causes, and are a result of poorly managed sensory information. In any case, we think it is worth exploring this possibility because, if the results of five and ten rehabilitation session are similar, it would be possible to reduce the cost of vestibular rehabilitation by half, which would also increase the chances of patients undertaking all the rehabilitation treatment.

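### Adherence, observed after randomisation, is on the covariate list of the efficacy model, so the adjusted treatment term no longer estimates the effect of assignment and can bias the five-versus-ten comparison

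*Protocol article*

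**What the plan says.** Under Analytical plan and statistical measures, the protocol article defines its covariates of interest as three groups: baseline characteristics from visit 0; risk factors (age, sex, weight, height, previous falls); and "Adherence to intervention", which the investigator observes directly. No scale is given for the third.

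Under Multivariate analysis, the model is introduced with this purpose: "In order to analyse the efficacy of the intervention in improving balance from the baseline". It takes in each subject's "repeated measures (visits 2, 3 and 4) and the covariables of interest, we will use mixed linear models", with treatment as a fixed factor.

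Arms A and C are assigned ten sessions and arms B and D five; arm B is described as "Same as Group A, except for the number of sessions (5) and their distribution". One secondary objective is "To assess whether the reduction in the number of vestibular rehabilitation sessions (five) leads to similar results" to ten sessions. The Discussion remarks that if five and ten sessions perform alike, cost could be halved, "which would also increase the chances of patients undertaking all the rehabilitation treatment".

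The analyses are based on all randomised eligible subjects. Under Bivariate analysis, changes in the balance tests are also compared between groups by ANOVA or Kruskal-Wallis, with no covariates.

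**The concern.** Adherence is observed while treatment is being given, so assignment can affect it. It is also likely to reflect traits such as frailty or motivation that affect balance. A model that holds it fixed compares patients in the five- and ten-session arms who ended up with the same adherence. Randomisation did not create those groups and does not protect the comparison between them. Part of any true effect of prescribing more sessions may also act through sessions attended, and adjustment removes that part.

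At stake is what the adjusted result means. The question is whether prescribing five sessions does as well as prescribing ten. A covariate that pulls the difference towards zero, or widens its interval, would make five sessions look similar for the wrong reason. A covariate that pushes the other way would make ten look better. The same applies to the device contrast if patients adhere differently to the two systems.

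**Working it through.** **Text.** The covariate list is a defined term, adherence is one of its three entries, and the efficacy model invokes the list as a whole. Nothing shown limits adherence to descriptive, per-protocol or sensitivity use.

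**Why scale matters.** The protocol gives no figure for this effect, so there is none to reproduce. In a linear model with arm and one covariate A,

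adjusted difference = (mean outcome, ten - mean outcome, five) - b × (mean A, ten - mean A, five),

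where b is the within-arm slope of outcome on A. The first bracket is the effect of assignment; the second term is what adjustment subtracts. It is zero if mean adherence is equal across arms, or if b = 0.

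- *Percentage of assigned sessions:* the arm means can be equal, and then there is no bias.
- *Count of sessions attended:* the means differ by design. At an assumed 90% attendance they are 9 and 4.5, a gap of 4.5. If each session attended is worth an assumed 1 point, the effect of assignment is 1 × 4.5 = 4.5 points, and the adjusted difference is 4.5 - 1 × 4.5 = 0.

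**Precision on the count scale.** With 110 v 110 (devices pooled) and an assumed residual SD of 15, the unadjusted SE is 15 × √(2/110) = 2.02. The average within-arm variance of sessions attended is (10 × 0.9 × 0.1 + 5 × 0.9 × 0.1)/2 = 0.675. The between-arm variance is 4.5²/4 = 5.06. Arm therefore explains 5.06/(5.06 + 0.675) = 0.88 of the covariate. The SE is multiplied by √(1/(1 - 0.88)), about 2.9, which gives about 5.9.

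**Simulation A** (SD 15; 220 patients; linear model with arm and adherence; any prognostic trait worth 3 points per SD, with 0.8 log-odds of attendance per SD). Ten minus five, in points:

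| Adherence scale and setting | Without adherence | With adherence |
|---|---|---|
| Count, no trait, 1 point per session | 4.5 | 0.2 |
| Count, trait, no session effect | 0.0 | -6.5 |
| Count, trait, 1 point per session | 4.4 | -6.7 |
| Percent, equal adherence, 1 point per session | 4.4 | 4.4 |
| Percent, lower with ten (about 80% v 90%), unrelated to balance | 0.0 | 0.0 |
| Percent, lower with ten, 1 point per session | 3.5 | 4.2 |
| Percent, lower with ten, trait, no session effect | 0.0 | 1.1 |

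**Simulation B** (no true effect; total SD 18.2). The protocol states no SD. The assumed value is close to what 53 per arm would imply for a 10-point difference at two-sided 0.05 and 80% power: 10 × √(53/2)/(1.96 + 0.84) = 18.4. Unadjusted SE: 18.2 × √(2/110) = 2.45. Attendance has log-odds 2.2, lowered in the ten-session arms by the amount shown, and 0.8 per SD of trait unless stated.

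| Setting | Bias, percent | Bias, count |
|---|---|---|
| Trait 6-9 points, log-odds lowered by 0.6-1.0 | +1.6 to +4.2 | -7.4 to -14.6 |
| Trait 3 points, log-odds lowered by 0.6-1.0 | +0.8 to +1.5 | -3.6 to -4.8 |
| Trait 3 points, log-odds lowered by 0.3 | about +0.3 | |
| Trait 6 points, trait-to-attendance 0.3, log-odds lowered by 0.6 | about +0.7 | |
| Equal attendance, trait 3-9 points | about 0 | -6.9 to -19.7 |

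Without adherence in the model, bias is about 0 throughout. On the count scale the SE is 3.4 to 4.2 in the first row and up to about 6.9 across the settings tried.

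**The case against.** A reader might infer that the five-versus-ten result is certain to be biased. The documents do not support that. No adherence scale is given, and on a percentage scale there is no bias if adherence is equal across arms. The large negative figures belong to the session-count reading alone, which the protocol does not state.

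A reader might also infer that the protocol itself predicts lower adherence with ten sessions. The Discussion remark is conditional and concerns completing the whole programme. Attending all of five sessions is easier than attending all of ten even when the chance of attending each session is the same. The remark makes a dependence on arm plausible but does not establish lower percentage attendance.

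Nor is every randomised comparison in the trial compromised. The ANOVA or Kruskal-Wallis comparison carries no adherence term, and five versus ten is a secondary objective.

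The simulations are also simpler than the planned model. They omit baseline SOT, TUG, DHI, Short FES-I, age and the other listed covariates, which could absorb part of a frailty effect. Every behavioural input is assumed, and at the weak end the percentage-scale bias (about +0.3 to +0.7) is small against an SE of 2.45.

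All of this stands as a limit on size and certainty. It does not remove the defect. Nor is this a detail left to an analysis plan: the article positively lists adherence and positively brings the list into the efficacy model.

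**Conclusion.** The point holds for the adjusted efficacy model. As written, that model conditions on a variable observed after randomisation, so its treatment term does not estimate the effect of assignment. This can bias the secondary five-versus-ten comparison, and the device comparison if adherence differs by device.

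The principle is firm; the size is not. With no true effect, an SD of 18.2 and a prognostic trait of 3 to 9 points per SD, all assumed, the bias is about 0 to +4 points in favour of ten sessions on a percentage scale and about -3 to -20 points on a count scale. On the count scale the loss of precision is substantial even without bias. For comparison, the sample size section refers to a 10-point change. Because the scale is not stated, even the direction of any bias is open.

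**What to change.** Remove adherence from the covariates of the efficacy model under Multivariate analysis. Keep the pre-randomisation covariates already listed: the visit-0 variables, age, sex, weight, height and previous falls. Report adherence descriptively by arm, with its scale defined. Put any question about adherence or completers in a separate analysis labelled supplementary.

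The cost is a wording change in the protocol or analysis plan. Sample size, visits and data collection are unchanged.
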